# Comparison of Sun Protection Factor (SPF) 30 Persistence Between Inorganic and Organic Sunscreen in Swimmers: Protocol for a Multicenter, Randomized, Noninferiority, Split-Body, Double-Blind Clinical Trial

**DOI:** 10.2196/42504

**Published:** 2022-12-21

**Keywords:** inorganic sunscreen, organic sunscreen, persistence, sun protection factor, sunscreen, swimmer, swimming

## Abstract

**Background:**

Outdoor swimming athletes are often exposed to undesirable environmental conditions such as long-term sun exposure. The risk of sunburn can still occur in this population due to the loss of sunscreen and an increase in the sensitivity of the skin to ultraviolet rays, particularly ultraviolet B, in wet conditions. Some previous trials showed that organic sunscreens had a longer shelf-life than inorganic sunscreens after exercise due to their characteristics to bind better with the skin layer. Meanwhile, inorganic sunscreens tend to form layers on the skin’s surface so that they can be more easily removed. To our knowledge, no studies evaluate sunscreens' resistance, either inorganic or organic, after exercising in Indonesia.

**Objective:**

This study aims to evaluate the persistence of inorganic versus organic sunscreens used by swimmers. The primary objective is to assess whether the inorganic sunscreen is as good as the organic sunscreen in the field of the persistence of sunscreens after swimming for 1.5 hours.

**Methods:**

This study is a randomized, split-body, double-blind, noninferiority, and multicenter clinical trial in Cikini, Jakarta, Indonesia. An estimated 22 athletes in each group, who aged 18-40 years and practice in the morning or afternoon, will be randomized using a computer-generated randomization method. We calculated the sample size using the difference in the average decrease in sun protection factor (SPF) levels that is considered significant based on the clinical judgment set by the researchers, which was 5. Neither the research subjects nor the researchers are aware of the type of sunscreen that will be applied. The hypothesis will be tested using paired-sample t test or Wilcoxon to assess the difference of SPF levels in each group between organic and inorganic sunscreens with SPSS (version 20.0; IBM Corp).

**Results:**

This study has been approved by the Ethical Committee Faculty of Medicine Universitas Indonesia and is funded by the International Publication Grant from Universitas Indonesia. The enrollment process was completed in December 2020.

**Conclusions:**

This study will test all procedures in preparation for conducting the main study, including several potential obstacles and challenges from the perspective of participating physicians and eligible swimmers. The study results will be disseminated through publications in a peer-reviewed journal with Open Access format. This study will provide information about SPF 30 persistence in sunscreens and the best type of sunscreen to be used while swimming, particularly for athletes.

**Trial Registration:**

ClinicalTrials.gov NCT04618536; https://clinicaltrials.gov/ct2/show/NCT04618536?term=NCT04618536

**International Registered Report Identifier (IRRID):**

RR1-10.2196/42504

## Introduction

Athletes who train and compete for outdoors such as in swimming pools are often exposed to undesirable environmental conditions, such as excessive humidity, hot and cold weather, windy conditions, and long-term sun exposure. These exposures cause some skin conditions [1]. In Indonesia, the average training time of an athlete is 5 times a week for 1.5-2 hours per day. Exercise is carried out in the morning and evening, when the ultraviolet index (UVI) was in the range of 1-4, meaning that taking shelter, wearing closed clothes such as hats, using sunscreen, and other sun protection manners should be done [2].

When swimmers train in an outdoor swimming pool, apart from being exposed to the pool water, they are also exposed to sun’s radiation. Water could wash away the applied sunscreen, increasing the risk of photosensitivity [3]. In addition, there will be an increase in humidity in the stratum corneum, which functions to protect the skin from ultraviolet (UV) radiation [4,5].

In order to prevent sunburn, sun protection is needed, which can be achieved in several ways, such as using a sunscreen [4]. There are 2 types of sunscreens used based on the filter component, specifically organic and inorganic sunscreens. Organic sunscreen absorbs and prevents UV light to enter the epidermis; meanwhile, inorganic sunscreen works by reflecting and scattering radiation [6-8].

Some previous trials showed that organic sunscreens had a longer shelf-life than inorganic after exercise due to its characteristics to bind better with the skin layer. Meanwhile, inorganic sunscreens tend to form a layer on the skin’s surface, so that it can be more easily removed. Until this time, there have been no previous studies regarding the resistance of sunscreens, either organic or inorganic, after exercising in Indonesia. Therefore, this study aimed to evaluate the persistence of sunscreen with a sun protection factor (SPF) 30 used by swimmers after 1.5 hours.

## Methods

### Study Aims and Objectives

First, this study aims to assess whether inorganic sunscreen is as good as organic sunscreen in the field of the persistence of sunscreens after swimming for 1.5 hours. SPF of inorganic and organic sunscreens will be calculated before and after swimming training. The difference between those times will be measured and compared. SPF will be quantified using the minimal erythema dose (MED) test that will be conducted in 2 days. Irradiation will be carried out on the first day, and MED results will be collected 24 hours after irradiation.

Second, we assess the SPF value resulting from in vivo method conducted before swimming. The SPF of either organic or inorganic sunscreens will be compared in the manner of MED. This trial also aims to know the decreasing level of SPF after swimming for 1.5 hours and which type of sunscreen provides higher persistence.

### Study Design and Setting

This is a randomized, split-body, double-blind, noninferiority, multicenter clinical trial. The recruiting center is Cikini swimming pool, located in Jakarta, Indonesia. Recruitment began in August 2020 and ended in December 2020.

Research subjects were selected from Cikini swimming center in Jakarta, Indonesia. Data collection will be carried out on the same person using the split-body method. Each research subject will receive 2 treatments in the form of inorganic and organic sunscreens. The sunscreen application will be executed on the back area on the right and left for each treatment simultaneously.

### Eligibility Criteria

Inclusion criteria are as follows: female or male swimming athletes aged 18-40 years, practicing swimming at least 3 times a week with a duration of 1.5-2 hours per practice in the morning or afternoon, willing to be the subject of research by signing the consent form, do not have skin diseases or a history of allergies to sunscreens.

Exclusion criteria were as follows: existence of skin lesions in the test area; undergoing phototherapy; using drugs with photosensitivity side effects; history of skin malignancy, photosensitivity reactions, or disease affected by UV rays; exposure to direct sunlight to the test area 24 hours before the study and during the study period; absence of an erythema response 24 hours after the radiation test; and erythema occurs in the entire test area box 24 hours after the radiation test.

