### Standard Treatment for the Management of Adverse Events

If side effects occur in the form of blisters, pain, edema, or bright red erythema after irradiation, the research subjects will be treated with normal saline compresses for 15 minutes twice a day. The compresses can be continued with topical corticosteroids twice a day after bathing. Research subjects who experienced side effects will be excluded from the study, but their development will continue to be followed until they recover.

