### Data Collection Methods

Before data collection begins, a preliminary study will be conducted to determine the value of broadband ultraviolet B (BB-UVB) MED on various skin types as well as to conduct inter-reviewer reliability tests. The data will be obtained from the literature and the tool guide and used as a source of information on the differences in the test doses upon irradiation. Therefore, a preliminary study will be conducted to equalize the dose of the irradiation test. Reliability testing will be performed to achieve same perception to assess erythema to ensure the quality of the data produced during the research. The test will be carried out by showing 11 skin photos to 3 assessors to determine the MED of each photo [11]. After that, the readings of the 3 assessors will be compared based on the intraclass correlation (ICC). An ICC value close to one, in this study set at 0.9, indicates that the reviewer has the same understanding of the MED reading so that, in the study, the MED reading can be carried out by the researcher.

We will use inclusion and exclusion criteria to select the research subjects. We will provide explanations about the purpose and research method before research subjects sign a consent form. There will be 2 sessions in the study: the first one for basic data collection and research sample selection and the second one for providing treatment and executing the randomization process.

After the consent form is signed, we will conduct history taking, physical examination, and documentation. History of systemic disease, skin disease, daily activities, malignancies, and family history will be recorded. We will assess the skin type and identify any skin lesion on physical examination.

This study will use metal halide UV enhanced lamp BB-UVB in the active spectrum of 290-320 nm (The Daavlin Lumera) for UVB radiation test. The device will be calibrated before every data collection.

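### Two exclusion rules rest on the erythema reading and are not limited to the session before randomization, so athletes could be removed by their own outcome

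*Protocol article*

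**What the plan says.** Eligibility Criteria lists two exclusions based on the 24-hour skin reading: "absence of an erythema response 24 hours after the radiation test; and erythema occurs in the entire test area box 24 hours after" irradiation. Neither names a session. The Interventions section describes irradiation with a 24-hour reading at both meetings. The same exclusion list holds a criterion that clearly runs on: "exposure to direct sunlight to the test area 24 hours before the study and during the study period".

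Standard Treatment for the Management of Adverse Events describes reactions in the form of "blisters, pain, edema, or bright red erythema after irradiation" and then states: "Research subjects who experienced side effects will be excluded from the study". Follow-up continues only until recovery. No session limit is given, and the Discussion repeats the exclusion.

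Data Collection Methods describes the two sessions: "the first one for basic data collection and research sample selection", and the second for treatment and randomization. Interventions and Outcomes make the second-session reading the source of the MED, and so of the SPF before and after swimming. Each area carries 6 irradiation spots. Noninferiority is judged by a one-sided upper confidence limit against 4 SPF units.

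**The concern.** At the second session, erythema is the outcome itself. An area with all 6 spots red has an MED at or below the lowest dose used. An area with none red has an MED above the highest dose. Both are valid but bounded measurements. Dropping athletes for either reason after randomization selects on the outcome, and in a split-body design it discards the other side too.

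The direction matters for a noninferiority claim. The Introduction expects inorganic sunscreen to come off more easily. If so, athletes with the largest losses would be removed mostly because of their inorganic side, and the observed difference would move toward zero. That raises the chance of declaring noninferiority wrongly. With 22 athletes, losing two or three in this way is not negligible.

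**Working it through.** **Step 1: which session do the rules reach?**

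- *Eligibility Criteria.* Three features point to the first session: the heading, the singular reference to one radiation test, and the sample-selection role given to that session. Participant Timeline agrees, since screening to allocation takes 7 days and the sessions are 7 days apart. Against this, no session is named, and the sunlight item shows that the list is not purely a baseline list.
- *Adverse-event section.* The trigger is a reaction after irradiation. Irradiation occurs at both sessions, so the rule as written reaches the second.

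**Step 2: the plan's own figure.** Sample Size Estimates gives 22 with power 0.9 and alpha 0.05, but no SD or dropout rate, so 22 cannot be reproduced. Solving backwards for the SD of the paired difference, with no dropout allowance:

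- Margin 4, one-sided 0.05: 4 × √22 / (1.645 + 1.282) = 6.41.
- Difference 5, two-sided 0.05: 5 × √22 / (1.960 + 1.282) = 7.23.

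**Step 3: illustration.** Everything beyond n = 22, the margin of 4 and one-sided 5% is assumed. Let D be the inorganic loss minus the organic loss. The losses are bivariate normal with a common SD of 5 or 7 and correlation 0.5, so SD(D) = SD × √(2 × (1 − 0.5)) = 5 or 7, close to the values in step 2. The true mean of D is 4, exactly at the margin. Noninferiority is declared when mean(D) + t(0.95, n−1) × s/√n is below 4. The plan's additional P > .05 condition is left out. An athlete is dropped when either loss exceeds a threshold set at the 95th, 90th or 80th percentile of inorganic losses. There were 40,000 simulated trials per case.

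| Inorganic sides beyond threshold | Mean D after exclusion (SD 5 / SD 7) | False noninferiority (SD 5 / SD 7) | Athletes lost | False noninferiority if all kept and the bound substituted |
|---|---|---|---|---|
| none excluded | 4.0 / 4.0 | 5% / 5% | 0 | n/a |
| 5% | 3.76 / 3.73 | 7.5% / 6.9% | about 1.2 | 5.8–5.9% |
| 10% | 3.60 / 3.55 | 9.9% / 8.6% | about 2.5 | 7.0–7.2% |
| 20% | 3.34 / 3.25 | 14.2% / 12.0% | about 5 | 10.5–11.7% |

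**Step 4: other assumptions** (20,000 trials each).

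- *Graded loss at the margin.* Pre-swim SPF 30, organic post-swim mean 22, between-athlete SD 4, within-site SD 3. Dropping athletes with a post-swim SPF below 10, 12 or 15 gives false noninferiority of 5.9%, 8.1% or 11.0%. Keeping everyone and substituting the floor gives 5.3%, 7.0% or 13.5%. Also dropping the no-erythema end gives 10.2% (SPF 12 to 30 kept) or 18.3% (15 to 28 kept).
- *All-or-nothing failure on the inorganic side only.* A 28.6% failure rate at 14 SPF units each gives a true mean of 0.286 × 14 = 4.0. The probability of declaring noninferiority is 6.4% with all kept and 91% after exclusion. This is an extreme case, because the excluded failures carry the whole difference.
- *Equal failure.* The mean stays at 0. The probability of declaring noninferiority, which is then the correct conclusion, moves from 0.92 to 0.89 (graded, cut 15) or from 0.76 to 0.94 (all-or-nothing, 10% per side).
- *Organic fails more (20% against 5%).* The probability falls from 0.97 to 0.93.

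**The case against.** A reader might infer that post-swim failures are certain to leave the analysis and that the result therefore drifts toward noninferiority. The documents do not support that.

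- The two erythema criteria are most naturally screening rules for the first session (step 1). On that reading they remove no post-swim reading. This stands, although the text does not say it.
- The adverse-event rule is a safety provision. Exclusion from the study does not expressly delete a reading already taken, and the analysis set may be defined in a document not shown. This also stands. But the article states an exclusion and nowhere says that such readings are kept.
- Bright red erythema is a stronger reaction than the just perceptible redness that defines the MED. It may come from a high dose step or, at the first meeting, from the unprotected area, so it is not by itself a marker of wash-off. Nor does a wholly red box prove that most of the sunscreen was lost, because the dose ladder is not given.
- The failure rates, SDs and correlation are assumed, and the simulated trigger is a large loss of SPF, which only approximates the written triggers.
- The direction is conditional: it needs the rules to act at the second session and the inorganic product to fail more.

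What remains is that neither rule is limited to the time before randomization, and the adverse-event rule as worded covers the randomized session.

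**Conclusion.** The point holds as a conditional one. Followed literally, the text allows whole pairs to be removed after randomization on the basis of the reading that supplies the endpoint. This is clear for the adverse-event rule and possible for the eligibility criteria. Under the protocol's own expectation that inorganic sunscreen is lost more easily, the bias favours noninferiority: false noninferiority of about 7% to 14% against a nominal 5% in the main illustration. That size rests wholly on the assumed inputs in step 3 and depends strongly on how failures are distributed. The mean is not biased when both products fail equally often, and the shift reverses when the organic product fails more.

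**What to change.** 1. In Eligibility Criteria, state that the two erythema criteria apply only to the first-meeting reading, before randomization.
2. In the adverse-event section, state that exclusion from further study procedures does not remove second-session readings already obtained from the primary analysis. Care of the athlete is unchanged.
3. Treat a wholly red area as MED at or below the lowest dose and an area without erythema as MED above the highest dose. Make the primary analysis one that handles this censoring, such as an interval-censored paired model, and add a worst-case sensitivity analysis. Substituting the bound and running the usual paired test is not enough: it still left false noninferiority at about 6% to 12% in the main illustration, and in the graded-loss model at the highest cut it did worse than exclusion (13.5% against 11.0%).

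The cost is two sentences of wording and one change of analysis method. The downside is that a few values are known only as bounds and the result then rests on a distributional assumption, which should be stated.

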### Interventions

This study used a sunscreen made by PT Paragon Technology and Innovation. Both sunscreens are made in the form of an oil-in-water emulsion with the addition of a film-forming layer to maintain their resistance to water. Both organic and inorganic sunscreens have been tested using a simulator to determine their SPF levels.

Interventions will be conducted according to research manual of operations (Multimedia Appendix 1). First, we will mark the area on the back. In each area, we will draw 6 circles as locations for the irradiation test. We will apply as much as 2 mg/cm^2^ sunscreen on each area within 2 stages, particularly at the first and second sessions. The sunscreen will be applied using a 1-cc syringe to cover all areas. After that, the sunscreen is spread using gloves, starting with circular and then followed by horizontal and vertical movements with light pressure. During the smearing process, the smearing finger remains in contact with the skin for 35 seconds ±5 seconds. Gloves are changed at each smearing of a different test area.

At the first meeting, the back is marked with 3 areas (Figure 1). Sunscreens are applied to 2 areas; meanwhile, 1 area is left without any sunscreen applied. After 20 minutes, the irradiation test is performed. The MED values were calculated 24 hours after irradiation to determine the SPF of each sunscreen. This procedure is carried out to take note of the basic data and the suitability of the SPF with data that are listed on the packaging.

**Figure 1 figure1:**
[figure not shown]
Study procedure at the first meeting.

The second meeting will be conducted 1 week after the first one. At the second session, the back is marked with 4 areas (Figure 2). Both types of sunscreens are applied to all areas, where 2 areas are for the test before swimming and the other 2 areas are for the test after swimming. After 20 minutes, an irradiation test is performed. Athletes were then asked to carry out the exercise for 2 hours. After completion, the athletes were asked to dry their body without using a towel. The MED values were calculated 24 hours after irradiation to determine and compare the SPF of each sunscreen before and after the swimming period. Swimming activities are carried out in the morning or evening when the UVI is in the range of 0-2.

The SPF measurement of pre- and postswimming was obtained using an in vivo method adapted with modifications from ISO 24444 in 2019 and COLIPA 2006 by bringing the instrument to the study site and in a room with a temperature of 18-26 °C. The back area will be marked into 3 sections measuring 8 cm×5 cm each. Each area will be marked with a 6×3 cm^2^ perforated sticker according to The Daavlin Lumera probe.

**Figure 2 figure2:**
[figure not shown]
Study procedure at the second meeting.

### Discontinuation of Study Medication

The study medication must be discontinued if a suspected anaphylactic reaction or there are serious adverse events on the MED test square such as pain and formation of blisters during its administration or if the patient participation consent is withdrawn.

### Standard Treatment for the Management of Adverse Events

If side effects occur in the form of blisters, pain, edema, or bright red erythema after irradiation, the research subjects will be treated with normal saline compresses for 15 minutes twice a day. The compresses can be continued with topical corticosteroids twice a day after bathing. Research subjects who experienced side effects will be excluded from the study, but their development will continue to be followed until they recover.

### Outcomes

This study will provide mean differences in SPF by 4 to establish noninferiority with a 95% lower confidence limit. The hypothesis will be tested using paired samples *t* test or Wilcoxon test to assess the difference of SPF levels in each group between organic and inorganic sunscreens. The difference in SPF level will be declared to be no different if the *P* value for the paired *t* test or Wilcoxon test is >.05, and the upper limit of the CI does not exceed 4 SPF level. The persistence of organic and inorganic sunscreens is assessed using the following parameters: (1) the MED is defined as the dose of UV radiation that induces just perceptible erythema on exposed skin 24 hours after irradiation. This MED result will be stated in mJ/cm^2^. (2) SPF is defined as the ratio of MED between protected and unprotected skin areas. The average SPF value from each type of sunscreen will be computed. The SPF value will be rounded up to one decimal in the index unit. (3) Persistence of SPF is defined as the lowest differences of SPF value before and after 1.5 hours swimming, stated in index unit.

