### Data Management and Statistical Methods

All data obtained on the research status will be recorded for further coding. The collected data will be analyzed using SPSS (version 20.0; IBM Corp). The analysis will be carried out in 2 stages: descriptive and inferential analyses. In descriptive analysis, each variable is explained according to the type of data. The distribution of numerical data is assessed by looking at the normality value. The distribution of normal data is displayed with the mean and SD values. Categorical data are displayed in the form of frequency and percentage tables. In the inferential stage, the hypothesis will be tested using paired *t* test or Wilcoxon test to assess the differences in the decrease in SPF levels in each group of inorganic and organic sunscreens, and between the 2 groups. We used a 1-sided CI approach in the statistical analysis. The mean difference in SPF will be no different if the *P* value for the paired *t* test is >.05, and the upper limit of the CI does not exceed 4 SPF.

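### The noninferiority rule names both a lower and an upper confidence limit, for two variables with opposite harmful directions, and no order of subtraction is given

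*Protocol article*

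**What the plan says.** **Limit.** Outcomes opens by giving a mean difference of 4 SPF "to establish noninferiority with a 95% lower confidence limit". Two sentences later it declares no difference when P exceeds .05 and "the upper limit of the CI does not exceed 4 SPF level". Data Management and Statistical Methods states that a one-sided confidence interval is used and again requires P > .05 and that "the upper limit of the CI does not exceed 4 SPF".

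**Variable.** Outcomes applies the paired test "to assess the difference of SPF levels in each group between organic and inorganic sunscreens". Data Management and Statistical Methods applies it "to assess the differences in the decrease in SPF levels in each group of inorganic and organic sunscreens, and between the 2 groups", but its decision sentence goes back to SPF without a qualifier: "The mean difference in SPF will be no different if the" P-value and upper-limit conditions are met. Sample Size Estimates works on the average decrease. Outcomes, item 3, defines persistence by the change from before to after swimming.

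**Direction.** Study Aims and Objectives makes inorganic the product under test and organic the comparator. No section says which product is subtracted from which. The word order is organic then inorganic in Outcomes, and inorganic then organic in the statistical section.

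**The concern.** A one-sided interval has one informative limit, so the choice of limit is the decision rule. Which limit protects against inferiority depends on the variable and on the order of subtraction. The text names both limits and both variables and leaves the order open. Some combinations that it allows therefore test against superiority of the inorganic product and leave inferiority unchecked. The primary conclusion, that inorganic is as good as organic, would then rest on a bound that a worse product meets easily.

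**Working it through.** **1. Which bound protects.** Margin 4 SPF. Level means post-swim SPF; decrease means pre minus post.

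| Variable | Order | Protects against inferior inorganic | Does not protect |
|---|---|---|---|
| Level | inorganic - organic | lower limit > -4 | upper limit < 4 |
| Level | organic - inorganic | upper limit < 4 | lower limit > -4 |
| Decrease | inorganic - organic | upper limit < 4 | lower limit > -4 |
| Decrease | organic - inorganic | lower limit > -4 | upper limit < 4 |

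Each limit is right in two rows and wrong in two. Two wrong-side cases lie close to the text. One is the upper-limit sentence in Outcomes read on SPF level as inorganic minus organic. The other is the opening sentence of Outcomes applied to the decrease as inorganic minus organic; that sentence carries no P-value condition.

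**2. The plan's own figure.** The stated 22 (power 0.9, type I error 0.05, difference 5) cannot be reproduced, because no SD or dropout rate is given. It can be solved backwards for the SD of the paired difference, ignoring dropout: SD = δ√22 / (z_α + 1.282), with √22 = 4.690.

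- δ = 5, two-sided: 23.45 / 3.242 = 7.2
- δ = 5, one-sided: 23.45 / 2.926 = 8.0
- δ = 4, two-sided: 18.76 / 3.242 = 5.8
- δ = 4, one-sided: 18.76 / 2.926 = 6.4

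Taken instead as two independent groups with SD 5, the two-sided calculation gives 2 × (5 × 3.242 / 5)² = 21.02, rounded up to 22. The paired SD is then 5√(2(1 - ρ)): 7.1 at a within-athlete correlation of 0, and 5.0 at 0.5. The range 4 to 8 used below is an assumption. Any dropout allowance inside the 22 would make the back-solved SDs smaller.

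**3. Wrong-side limit, inorganic truly 4 worse, 22 pairs.** Take the level as inorganic minus organic (true mean -4) and an assumed SD of 6.

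- Standard error = 6 / 4.690 = 1.279.
- The upper limit is below 4 when the observed mean is below 4 - 1.721 × 1.279 = 1.80. That is (1.80 + 4) / 1.279 = 4.5 standard errors above the truth, so the condition is almost always met.
- P > .05 requires the observed mean to lie above -2.080 × 1.279 = -2.66, about 1.05 standard errors above the truth. The probability from the noncentral t distribution is 15%.

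Simulation, checked against the noncentral t distribution, gives:

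| Assumed paired SD | Wrong-side limit met | Wrong-side limit and P > .05 | Correct bound |
|---|---|---|---|
| 4 | 100% | 0.6% | 5% |
| 5 | 100% | 5% | 5% |
| 5.8 | 100% | 13% | 5% |
| 6.4 | 100% | 20% | 5% |
| 7.2 | 100% | 30% | 5% |
| 8 | 99.8% | 39% | 5% |

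The third column is, to within rounding, the chance of P > .05 alone. The wrong-side limit adds nothing to it. For a product worse by 10, the wrong-side limit is still met in 100% of trials, and the joint rule accepts in about 0%.

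**The case against.** The strongest defence is that the documents lean towards the decrease. The aims compare before-to-after differences, persistence is defined that way, the sample size rests on it and the statistical section tests it. For the decrease as inorganic minus organic, the upper limit below 4, stated twice, is the right bound. It is also right for SPF level taken as organic minus inorganic, which is the word order in Outcomes. On this view the only error is the phrase about a lower limit. This stands as far as it goes: a sound reading is available and is probably the intended one. It does not remove the conflict inside Outcomes, nor the change of variable between sections.

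A reader might infer that the rule as written accepts an inferior product nearly always, or more readily the worse it is. The documents do not support that for the upper-limit sentences. They join the limit to P > .05, so acceptance falls as the deficit grows. The 99.8-100% describes one half of a joint condition. Nor do the documents show that Outcomes puts the limit on the wrong side: that needs SPF level and inorganic minus organic together, and the combination is not stated. The 13-39% at SDs of 5.8 to 8 comes from treating non-significance as evidence of noninferiority. It shows that the wrong-side limit offers no protection of its own.

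A fuller protocol or analysis plan might give the order of subtraction. That would settle the direction, but the sentences printed here would still disagree.

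**Conclusion.** The decision rule contradicts itself as written. It names both limits, moves between two variables with opposite harmful directions, and gives no order of subtraction to choose between the readings. Some readings are valid and others leave inferiority untested by the interval.

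The size depends on the reading and on an SD that the protocol does not give. On the coherent reading the interval bound holds the error at 5%. On the upper-limit reading with the wrong side, false acceptance at a true deficit of 4 SPF is at or below about 5% for a paired SD of 5 or less, and rises to about 39% at 8. On the lower-limit reading of the decrease, taken as inorganic minus organic, no P-value condition applies and 99.8-100% would pass. These figures assume 22 complete pairs, normal differences, a paired t test and one-sided 95% limits. The primary claim turns on this rule, so the wording needs to be settled before noninferiority is claimed.

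**What to change.** - Define for each athlete D = (pre - post) on inorganic minus (pre - post) on organic. Declare noninferiority if the one-sided 95% upper limit of mean D is below 4.
- Delete the lower-limit wording from the first sentence of Outcomes.
- Remove P > .05 as a condition for noninferiority. It tests equality, is easier to meet with noisier data, and on the coherent reading would also deny the claim to an inorganic product that is significantly better.
- If post-swim SPF is also reported, use inorganic minus organic with the lower limit above -4.
- Make Outcomes and Data Management and Statistical Methods state the same rule, and name the same variable in the Methods paragraph of the Abstract.

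The cost is wording only. The Results section dates data analysis to January-March 2021, so the report should also say which variable, direction and limit were fixed beforehand, and give the result against that rule.
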